#### 2.6.2. Secondary Exploratory Outcomes

Secondary outcomes will be exploratory and include the following:Pulse rate and respiratory rate during treatment;Autonomic nervous system activity assessed via RR interval analysis;Stress-related electroencephalographic alpha wave activity;Patient-reported comfort and anxiety assessed using a nine-item questionnaire.

#### 2.6.3. Statistical Analysis

As this is a pilot feasibility study, formal hypothesis testing is not planned. Feasibility and exploratory outcomes will be summarized descriptively. Analyses of secondary outcomes will be exploratory and intended to inform the design of future definitive trials. Regarding continuous outcomes, we will estimate the mean difference between treatment with a HFNC and treatment without a HFNC, along with its 95% confidence interval.

In the case of missing data, the proportion of missing values will be reported for each variable at each time point. Summary statistics will be calculated excluding missing values. Differences between time points will be assessed after excluding subjects with missing values, as this study will include only two time points.

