## Abstract

**Background:** Dental treatment often requires prolonged mouth opening. This may compromise comfort during spontaneous nasal breathing and saliva swallowing, leading to stress or anxiety. A high-flow nasal cannula (HFNC) delivers warmed and humidified air at high flow rates and may improve breathing comfort; however, the feasibility of its routine use during dental treatment has not been established. **Objectives:** The primary objective of this pilot study is to evaluate the feasibility of conducting a definitive clinical trial to investigate the use of a HFNC during dental treatment. The secondary objective is to explore preliminary patient-centered outcomes related to stress and comfort to inform the design of future clinical trials. **Methods:** This single-center, open-label pilot feasibility study will be conducted at Nagasaki University Hospital, with adult patients undergoing routine full-mouth periodontal treatment participating in two treatment sessions, one without a HFNC and one with a HFNC, separated by at least four weeks. The primary feasibility outcomes include recruitment and retention rates, patient tolerance and acceptability of the HFNC, completeness of data collection, and device-related adverse events. The secondary outcomes are exploratory and include physiological stress-related parameters (pulse rate, respiratory rate, autonomic nervous system indices, and electroencephalographic alpha wave activity) and patient-reported comfort assessed using a questionnaire. **Conclusions:** This pilot study was designed to assess the feasibility and safety of HFNC use during full-mouth periodontal treatment and to inform the design of future definitive clinical trials. In particular, the resultant exploratory patient-centered outcomes and preliminary data may be used to guide outcome selection and sample size estimation.

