## 2. Methods

### 2.1. Study Design

This is an investigator-initiated, single-center, open-label pilot feasibility study that will be conducted at Nagasaki University Hospital, Japan. The study was designed in accordance with the Consolidated Standards of CONSORT extension for pilot and feasibility trials and the principles of the Declaration of Helsinki. Ethical approval was obtained from the Clinical Research Review Board of Nagasaki University, and the study is registered with the Japan Registry of Clinical Trials (jRCTs072240099). Given the exploratory nature of the research question and the need to evaluate feasibility-related parameters before a definitive trial, a pre–post, fixed-sequence, within-subject feasibility design was adopted.

As illustrated in Figure 1, this pilot study was specifically designed as a feasibility-oriented, pre–post, fixed-sequence, within-subject study to evaluate the practicality, acceptability, and safety of high-flow nasal cannula (HFNC) use during routine full-mouth periodontal treatment, rather than to assess clinical effectiveness. Participants will undergo two dental treatment sessions, one without a HFNC and one with a HFNC, separated by a washout period of at least four weeks.

The research design, measurement items, and evaluation indicators for high-flow nasal cannula (HFNC) intervention in full-mouth periodontal treatment are shown in Figure 1, which illustrates the structured approach to evaluating the impact of a HFNC during full-mouth periodontal treatment in a fixed-sequence, pre–post, within-subject feasibility design.

Research design (Pre–Post, Fixed-Sequence, Within-Subject Feasibility Design): The study will be conducted in two sessions separated by a washout period of 4 weeks.

Session 1 (Baseline Data Collection): Dental treatment will be performed under standard conditions without a HFNC to establish baseline physiological and psychological data.

Session 2 (HFNC Intervention): Dental treatment will be performed while delivering 20–30 L/min of heated and humidified air via a HFNC to measure the intervention’s impact.

Measurement items: Data collected include physiological indicators such as Pulse Rate (PR), Heart Rate Variability (HRV: LF/HF), Respiratory Rate (RR), and Brain Waves (EEG alpha), as well as patient-centered metrics like Quality of Life (QOL) and Satisfaction.

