### 2.5. Study Procedures

After providing informed consent, participants will undergo full-mouth periodontal treatment (approximately less than 30 min in the supine position without a rubber dam under High-Capacity Dental Suction conditions) in two different sessions. During the first session, full-mouth periodontal treatment will be performed without the use of a nasal cannula or other respiratory devices. Participants will subsequently complete a self-administered questionnaire. In the pre–post, fixed-sequence, within-subject feasibility design, stress during the second session may decrease independently of the HFNC due to factors such as habituation, reduced treatment volume/invasiveness, and changes in psychological adaptation. Therefore, the following points will be carefully considered. The two sessions will be conducted and standardized at the same time of day, by the same operator with five years of clinical experience using same instrumentation type with consistent treatment extent and duration, and each session involves the treatment of only one side of the jaw or one quadrant within the full-mouth periodontal treatment area in a total of two sessions. In addition, to minimize the possibility of marked changes in periodontal status by the second session, the interval between the two sessions will be limited to within four weeks.

The second full-mouth periodontal treatment session will be scheduled for at least four weeks after the first session. During this session, full-mouth periodontal treatment will be performed with a dedicated HFNC (AIRVO3, Fisher & Paykel Healthcare Ltd., Auckland, New Zealand). Prior to the start of treatment, the nasal cannula will be inserted into both nostrils, and warmed and humidified air will be delivered at an initial flow rate of 20 L/min. If no discomfort is reported, the flow rate will be gradually increased to a maximum of 30 L/min. The AIRVO3 HFNC will be applied with fixed FiO_2_ at 0.21 at a temperature of 37 °C, with appropriate matched cannula size (S, M, L size) for all patients and criteria for flow escalation and discontinuation.

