## 4. Conclusions

This RCT study is designed to assess the feasibility, acceptability, safety, and preliminary physiological effects of HFNC during periodontal treatment. By focusing on feasibility-related outcomes and exploratory patient-centered measures, this pilot study provides a methodological and physiological rationale for conducting a fully powered clinical trial to evaluate the effectiveness of the HFNC for improving breathing comfort and reducing treatment-related stress in routine dentistry in future-oriented studies.

These findings may suggest that delivering warmed and humidified high-flow air may address common sources of discomfort during dental treatment, particularly difficulties related to nasal breathing and swallowing saliva, which may contribute to dental anxiety. Although no conclusions regarding clinical effectiveness can be drawn from this exploratory pilot study, the results support subsequent confirmatory trials.

Ultimately, further research informed by these feasibility data has the potential to establish the HFNC as a novel, low-burden, patient-centered adjunct to routine dental care, with implications for improving treatment tolerance, safety, and overall oral health outcomes.

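### The contrast in section 2.6.3 is labelled HFNC versus no HFNC but is fully aliased with session order, nothing bars its use as an effect size, and the Conclusions wrongly call the study an RCT

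*Protocol article*

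**What the plan says.** Section 2.1 of the protocol article states that "a pre–post, fixed-sequence, within-subject feasibility design was adopted". Session 1 is described as follows: "Dental treatment will be performed under standard conditions without a HFNC to establish baseline physiological and psychological data". Session 2 is given with HFNC to every participant. There is no randomisation and no second sequence.

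Section 2.6.3 plans no formal hypothesis test. For continuous outcomes it states: "we will estimate the mean difference between treatment with a HFNC and treatment without a HFNC, along with its 95% confidence interval".

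Section 2.5 acknowledges that "stress during the second session may decrease independently of the HFNC due to factors such as habituation", and adds reduced treatment volume and psychological adaptation. Its answer is to standardise time of day, operator, instruments, extent and duration.

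On later use, the Abstract says "preliminary data may be used to guide outcome selection and sample size estimation". The Introduction, 2.1 and Limitations say much the same of the exploratory outcomes.

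Section 4 opens with "This RCT study is designed to assess the feasibility, acceptability, safety, and preliminary physiological effects of HFNC during periodontal treatment" and later says that "the results support subsequent confirmatory trials".

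On extent, 2.5 speaks of full-mouth treatment in two sessions and then says "each session involves the treatment of only one side of the jaw or one quadrant within the full-mouth periodontal treatment area". Limitations again describes the first session's treatment as full-mouth.

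**The concern.** The name given to the contrast in 2.6.3 attributes it to HFNC. With a fixed order it equally reflects habituation, expectation, the novelty of the device and anything else that differs between a first and a second visit. The 95% interval covers sampling error only and makes no allowance for these.

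Two things are at stake. First, readers may take the interval as a range for the HFNC effect. Second, planners of the definitive trial may take the point difference as its target effect. It is the only comparative estimate that 2.6.3 names, and no sentence restricts its use. The RCT label in section 4 adds to this by claiming a randomisation that the design lacks.

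**Working it through.** **The plan's own figure.** The target of 30 rests on the annual number of eligible patients. It has no effect size, alpha or power behind it, so there is nothing to reproduce.

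**Identifiability.** For participant i, write the session 2 minus session 1 difference as D_i = τ + π + e_i, where τ is the HFNC effect and π the session effect. The mean of D estimates τ + π.

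A model with 30 participant effects, one session term and one HFNC term has 32 columns:
- Fixed sequence as planned: rank 31, and the correlation between HFNC and session is 1.0. τ and π cannot be separated.
- Two sequences of 15 + 15, for comparison: rank 32, correlation 0. They can be separated if there is no carry-over.

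Standardising operator, time of day and instruments does not set π to zero, because habituation occurs under identical conditions. The interval between sessions does not help either: session 1 contains no HFNC, so there is no HFNC carry-over to wash out. The within-session percent changes in 2.5 remove differences in starting level, but comparing them between sessions is still a comparison of session 2 with session 1.

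**What the interval covers.** In units of the SD of paired differences, the half-width is t(0.975, n−1)/√n.
- n = 30: 2.045/5.477 = 0.37.
- n = 21 (the 70% retention criterion, 0.70 × 30): 2.086/4.583 = 0.46.

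With a session effect of δ SD in either direction, coverage of τ is P(|T| < t), where T is noncentral t with noncentrality δ√n. The documents give no δ, so these values are assumptions:

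| δ (assumed) | n = 30 | n = 21 |
|---|---|---|
| 0 | 95% | 95% |
| 0.10 | 91.7% | 92.8% |
| 0.25 | 73.7% | 80.6% |
| 0.50 | 24.6% | 41.3% |

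**If the point difference were used to size the next trial.** For a paired or crossover trial at two-sided 5% and 80% power, n = ((1.96 + 0.842)/d)² = 7.85/d². If a share f of the observed d is session effect, the true effect is d(1−f), and n rises by 1/(1−f)². With an assumed observed d of 0.5, the trial would be sized at 7.85/0.25 = 31.4, so 32:

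| f (assumed) | true d | n needed | power of a trial of 32 |
|---|---|---|---|
| 0 | 0.500 | 32 | 81% |
| 25% | 0.375 | 56 | 56% |
| 50% | 0.250 | 126 | 29% |
| 75% | 0.125 | 503 | 10.5% |

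Power is Φ(true d × √32 − 1.96); for f = 50%, Φ(1.414 − 1.96) = 0.29. With an observed d of 0.3 the sizes are 88 against 156, 349 and 1,396. With 0.8 they are 13 against 22, 50 and 197.

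The error can also go the other way. If unease with the new device masks part of the effect, f is negative. At f = −25% the factor is 1/1.25² = 0.64, and 31.4 × 0.64 = 20.1, so 21 would suffice where 32 were planned.

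**What remains usable.** If π is roughly constant across participants, it drops out of the variance of D, and the SD of paired differences can be carried forward. If habituation varies between participants, that variation enters the SD and enlarges it.

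**The case against.** The strongest reply is that the protocol already says most of this. Section 2.1 states that clinical effectiveness is not the aim. Section 2.5 names the reasons why stress may fall anyway. Limitations concedes sequence, period, learning and expectation effects and says a randomised crossover would suit better. Section 2.6.3 tests no hypothesis, and its second paragraph speaks of comparing time points. The sentence in section 4 about supporting further trials itself disclaims any conclusion on effectiveness. All of this stands: the confounding is not hidden. What the disclosures leave undone is to correct the name of the estimate in 2.6.3 or to limit its use.

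Several stronger readings are tempting but not supported:
- *The mean difference will be the next trial's assumed effect.* No sentence says so. The documents speak of preliminary or exploratory data in general, and using only the SD and completeness would satisfy every one of those statements.
- *The difference will be inflated.* Section 2.5 says only that stress may fall. Limitations explains that the order was chosen to limit anxiety about HFNC, so the device's novelty could push the other way.
- *The lack of a parallel arm rules out the RCT label.* A randomised crossover has none either. The label fails only because nothing is randomised.
- *The closing claim cancels the feasibility criteria.* The thresholds in 2.6.1 stand unchanged.
- *Treatment extent differs between a participant's sessions, or a different site is treated.* Section 2.5 requires consistent extent, and a change of site is at most implied. The wording is loose rather than proof of unequal treatment.

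**Conclusion.** The point holds in limited form. The contrast in 2.6.3 is completely aliased with session order. That follows from the design and needs no assumption. The label attributes it to HFNC, and no text prevents its use as an effect size. RCT in section 4 contradicts 2.1 and Limitations, and the statement that the results support confirmatory trials is premature for a study that has yet to be conducted.

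The size of any harm is conditional. It arises only if the point difference is used for planning, and then follows 1/(1−f)², with f not given in the documents and of either sign. The coverage and sample-size figures are illustrations under assumed values, not predictions. The feasibility outcomes, which are the primary purpose, are unaffected. The corrections should be made because they govern what the study may conclude, but the design can stay as it is.

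**What to change.** 1. In 2.6.3, name the contrast *session 2 (with HFNC) minus session 1 (without HFNC)* and state that it does not estimate the HFNC effect.
2. In the same place, state that only the SD of paired differences (assuming a roughly constant session effect) and data completeness, not the point difference, will inform the next trial's sample size. How that trial chooses its target effect and allows for uncertainty in the SD can be left to its own protocol.
3. In section 4, replace RCT with *single-group, fixed-sequence feasibility study*, and make support for a confirmatory trial conditional on meeting the 2.6.1 criteria.
4. Reconcile the descriptions of treatment extent in 2.5 and Limitations. Extent is one of the controls that 2.5 relies on against session effects, so its definition should be unambiguous.

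The cost is text only. Recruitment, visits and measurements do not change. The downside is that the study reports no HFNC effect estimate, which this design cannot provide anyway.

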No waveform correction will be performed during measurements using either the MWM20 EEG or ECG monitor. In the dental treatment setting, swallowing, mandibular movements, instrument noise, and body motion may also further interfere with EEG α-wave recordings. Therefore, the protocol restricts measurements to standardized short resting periods (an approximately two-minute resting state) for stable measurement before and after treatment rather than during instrumentation itself. It should be noted that the minimum valid recording length required for EEG α-wave analysis will be maintained for at least two minutes, with no large spikes in waves. All the participants must avoid swallowing saliva, opening or closing the mouth, and body movement during the measurement. In EEG (electroencephalogram) data, sections with noise may show large spikes in delta waves. In EEG data, sections with noise may show large spikes in EEG waves.

This is primarily believed to be caused by significant electromyographic activity, such as body movements or blinking. In MW2, data is output using 4 s windows shifted by 2 s.

This is then averaged over 10 s and exported as a CSV file. Since the numerical values in noisy sections change significantly for only an instant, removing those sections afterward serves as a method to address noise and artifacts. The EEG α-wave activity will be expressed as a mean appearance rate during a predefined resting window. In this feasibility study, the evaluation of EEG α-wave analysis would be a highly exploratory feasible measure.

The baseline value will be established prior to the intervention, and signal analysis will be performed using automated analysis with MemCalc™.

The protocol will be stopped if a significant risk to the research subjects or extreme discomfort is identified. For example, if patients experience adverse events such as epistaxis, discomfort, aspiration/cough events, or desaturation according to vital sign monitoring, the principal investigator should adjudicate the AEs and should stop the protocol.

In this study, safety and infection control in the dental operatory require explicit handling. HFNC therapy introduces airflow, humidification, and interface equipment in a setting with aerosols and cross-infection risk. We will use a single-use circuit and cannula with a built-in filter device. After completion of each session, the AIRVO3 machine will be decontaminated using a special cleaning circuit.

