### 2.6. Outcomes (Table 1)

#### 2.6.1. Primary Feasibility Outcomes

The primary feasibility outcomes are as follows:Recruitment ≥ 5/month (30 cases/6 months);Retention rates ≥ 70%;Patient tolerance and acceptability of the HFNC during dental treatment ≥ 80%;Completeness of physiological and questionnaire-based data collection ≥ 80%;Occurrence of device-related adverse events at less than 5% (less than one case).

**Table 1 dentistry-14-00208-t001:** Outcomes table.

Category	Outcome	Purpose
Primary (Feasibility)	Recruitment, retention	Trial feasibility
	Acceptability, tolerance	Practical implementation
	Data completeness	Outcome feasibility
	Adverse events	Safety
Secondary (Exploratory)	Pulse rate, respiratory rate	Stress physiology
	HRV (LF/HF)	Autonomic response
	EEG alpha activity	Neurophysiological stress
	Questionnaire	Patient-centered outcomes

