#### 2.6.4. Sample Size

As this is a pilot feasibility study, a formal sample size calculation based on statistical power was not performed. Approximately 30 patients per year who meet the eligibility criteria are treated at the Department of Special Care Dentistry of Nagasaki University Hospital. Therefore, a target sample size of 30 participants was considered feasible within the planned study period and sufficient to assess feasibility outcomes, including recruitment, acceptability, data completeness, and safety, to inform the design of future definitive trials.

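### The session comparison uses complete pairs only, justified by there being two time points; that reason does not make deletion valid, and the 80% completeness criterion has no stated denominator

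*Protocol article*

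**What the plan says.** Section 2.6.3 plans an estimate, with 95% confidence interval, of the mean HFNC minus no-HFNC difference for continuous outcomes. Its missing-data rule for that comparison is: "Differences between time points will be assessed after excluding subjects with missing values, as this study will include only two time points". It adds that "the proportion of missing values will be reported for each variable at each time point".

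Section 2.6.1 lists separate feasibility criteria, including "Retention rates ≥ 70" per cent, "Patient tolerance and acceptability of the HFNC during dental treatment ≥ 80" per cent and "Completeness of physiological and questionnaire-based data collection ≥ 80" per cent. No unit (patient, pair, session or variable) and no denominator is given for completeness.

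Section 2.5 fixes the order: session 1 without HFNC, session 2 with it. It has participants fill in a questionnaire after treatment. For events such as epistaxis, discomfort, cough or desaturation it says "the principal investigator should adjudicate the AEs and should stop the protocol". It does not say what happens to data from a session that is stopped.

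Section 2.6.4 sets the size: "a target sample size of 30 participants was considered feasible within the planned study period".

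**The concern.** The article gives a reason for deletion, and the reason is wrong. Two time points make complete-pair analysis simple, but they do not make it unbiased. That requires that whether a participant has both values is unrelated to how much that participant changes between sessions.

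The design gives grounds to doubt this. Because the order is fixed, anyone who does not return loses the HFNC value and never the control value. Non-return may depend on how stressful session 1 was. Loss during session 2 may depend on how HFNC was tolerated. Both are close to the outcomes being compared.

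The Introduction and Limitations say that these data will guide outcome selection and sample size for a definitive trial, so a mean difference from a selected subset would be carried forward. Separately, a primary feasibility criterion whose denominator is open can pass or fail on the same data, according to a choice made afterwards.

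**Working it through.** **Inputs.** Target 30 (section 2.6.4; also 5 per month × 6 months = 30 in section 2.6.1). Retention threshold 0.70 and completeness threshold 0.80 (section 2.6.1). Assumptions: retained means attending session 2, and all 30 attend session 1.

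**1. Size of the paired set and precision.**
- Retained at the threshold: 0.70 × 30 = 21.
- If 80% completeness is counted among those retained: 0.80 × 21 = 16.8, so 17 complete pairs, which is 17/30 = 57% of those enrolled.
- Half-width of the 95% interval, in SD of the paired difference, is t(0.975, n−1)/√n: 0.37 for n = 30, 0.46 for n = 21, 0.51 for n = 17.

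**2. Bias when loss is related to the change itself** (for example intolerance in session 2). Bias of the complete-pair mean = q × d, where q is the share excluded and d is the difference in mean change between completers and excluded. The documents give no d, so a range is assumed:

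| q | d = 0.25 SD | d = 0.5 SD | d = 1.0 SD |
|---|---|---|---|
| 0.20 | 0.05 | 0.10 | 0.20 |
| 0.30 | 0.075 | 0.15 | 0.30 |

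If those lost did worse on HFNC, this error favours HFNC.

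**3. Bias when loss is related to session 1.** Assume normal scores with equal SD in both sessions and correlation ρ, and an extreme case in which the 30% most stressed at session 1 do not return. The remaining 70% have a session 1 mean of −φ(0.524)/0.70 = −0.348/0.70 = −0.497 SD. Expected change given session 1 moves by (ρ − 1) × session 1, so the complete-pair change shifts by (1 − ρ) × 0.497:
- ρ = 0.3: 0.35 SD
- ρ = 0.5: 0.25 SD
- ρ = 0.7: 0.15 SD

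On a scale where higher is worse, this shift makes HFNC look worse. Steps 2 and 3 have opposite signs, so the direction of bias cannot be known in advance. A random-participant model fitted to all available values corrects step 3, because loss there depends only on an observed value. It does not correct step 2.

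**4. Ceiling on completeness at 21 of 30 retained.**

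| Reading of completeness | Ceiling | Can 80% be met? |
|---|---|---|
| Complete pairs, or session 2 data, per enrolled patient | 21/30 = 70% | No (24/30 needed) |
| Session records pooled over both sessions, all enrolled | (30 + 21)/60 = 85% | Yes (48/60 needed; 3 to spare, so 48/51 = 94% of attended records usable) |
| Retained patients only | 21/21 = 100% | Yes (17/21) |

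Retention of 22 or 23 gives the same split; from 24 of 30 all three readings can pass. With independent dropout, the chance of retaining 21 to 23 (retention passes, paired completeness cannot) is P(≥21) − P(≥24). It is 0.589 − 0.160 = 0.43 if true retention is 70%, 0.939 − 0.607 = 0.33 at 80%, and about 0.03 at 90%.

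**The case against.** Three stronger readings are tempting, and the documents do not support them.

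- *Participants whose HFNC is stopped are deleted.* The rule acts on missing values, not on stopping. Section 2.5 asks for a questionnaire after treatment without excepting stopped sessions, and pulse and respiratory rate are means over the procedure, which a shortened session can still supply. The text is silent; it does not remove these participants.
- *At 70% retention the 80% criterion cannot be met on enrolled patients.* This is true for pairs or session 2 data, but false for pooled session records, where the ceiling is 85% with all 30 enrolled in the denominator. The two criteria are separate minimums and can both be met. The defect is an undefined denominator, not a contradiction.
- *Deletion necessarily flatters HFNC.* Step 3 of the working shows that loss driven by session 1 stress pushes the other way.

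The defence also has substance. The affected comparison is exploratory, without hypothesis testing. Missing proportions will be reported by variable and time point, and retention, tolerance and device-related events are primary outcomes in their own right, so intolerance would be visible. Signal artefact is another expected cause of missing values. A mixed model does not repair loss caused by intolerance in session 2. An article may also leave analysis detail to a fuller document.

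What remains is that this article states a rule and a reason, and the reason is invalid. Reporting how much is missing does not correct the estimate. The limit of the model is why the questionnaire for all who start session 2 is needed beside it.

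**Conclusion.** The point holds as a wording and analysis weakness that should be corrected; it does not undermine the feasibility aim. Complete-pair deletion is not justified by having two sessions. Under the assumptions shown, it could shift the exploratory difference by about 0.075 to 0.30 SD if 30% are excluded because of how they respond, or by about 0.15 to 0.35 SD in the extreme case of loss driven by session 1, with opposite signs. These are illustrations: the documents give no SD, no correlation and no pattern of loss. If retention is high, both the bias and the denominator problem become small.

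The completeness point is secondary and rests on arithmetic alone: between 21 and 23 retained, whether a primary feasibility criterion can be met depends on a denominator that is not stated.

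**What to change.** 1. Delete the two-time-points reason in section 2.6.3.
2. For continuous outcomes, estimate the session difference from all available data with a mixed model (session fixed, participant random), valid under missing at random, and give complete pairs as a sensitivity analysis. The participant effect must be random: with fixed effects, those seen once add nothing to the contrast.
3. Tabulate session 1 values for participants with and without session 2 data.
4. State that everyone who starts session 2 is given the questionnaire, including when HFNC is stopped, and that data recorded before a stop are kept and analysed.
5. In section 2.6.1, define the unit and denominator of completeness in advance (for example per variable over sessions attended), and report the figure over all enrolled beside it.

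The cost is a few sentences, a few lines of code, and a questionnaire for the few who stop early. No change to sample size or schedule is needed.
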